#### Post-hoc analyses

Post-hoc analyses will be conducted to attempt to ascertain what factors predicted better responders among the two treatment arms. Potential prognostic factors include gender, tobacco, anxiety, depression, (age and past back pain history will be assessed for residual confounding, but controlled in study design), belief in effectiveness of the treatments, NSAID use, rescue acetaminophen use.

#### Other considerations

The primary and main secondary analyses will be performed using an intent-to-treat strategy in which patients are analyzed based on their randomized assignment irrespective of their compliance to the treatment protocol. Formal interim analyses of efficacy will not be conducted. However, the operational aspects of the study (recruitment, retention, adherence rates, and rates of missed visits) will be monitored as the study progresses so that corrective action may be taken to address any unexpected difficulties. Monitoring for safety will be conducted throughout the study, investigating all possible unanticipated safety events, including increased pain and discomfort which are the two most likely types of events to occur. These treatments are widely used and are considered safe with low rates of adverse effects. Efforts will be made to minimize the rates of missing data, including telephone follow-up of missed visits. The restricted maximum likelihood procedure of the primary analysis produces approximately unbiased estimates of the treatment effects so long as data are missing at random [42] and is less sensitive to missing data than analyses restricting to complete data [43]. In sensitivity analyses, multiple imputation incorporating baseline and follow-up predictors of outcome [44] will be used to assess the effect of potential violations of the missing at random assumption.

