### Statistical analysis

#### Primary analysis

The primary analysis is the comparison of the three study arms on the primary outcome, Oswestry Disability Index (ODI). Given that repeated measurements are collected, a mixed effects linear regression model will be fitted with an unstructured covariance matrix to account for lack of independence introduced by the repeated measurements. In this model, the repeated measurements are nested within study subject (weeks 0, or baseline, and weeks 1, 4, 8, and 12). The primary predictor is study group. A time variable will be included as a covariate, since visits will not always be at the planned intervals. Other covariates will be assessed for possible confounding in the relationship between treatment arm and outcome. It is likely that the pattern of dropouts will vary between the study groups, where the study interventions that are most effective having the dropouts later on in the follow-up, while the intervention least effective to have dropouts early on. The analysis will emphasize the 4-week time point as the primary end point, which ends the intensive intervention period. At 4 weeks compliance to the protocol and complete follow-up should be at a maximum. The remaining time to 12 weeks will measure long term effectiveness and acceptance of the study interventions.

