## Discussion

Chronic low back pain is a significant issue, resulting in significant costs, lost productivity, and morbidity [1-6]. Therefore, even small improvements in treatment efficacy, particularly for treatments with few side effects, can have a meaningful impact on improving LBP. While there have been some studies assessing the therapeutic effectiveness of TENS, the effect generally is relatively small improvements in chronic LBP as compared to sham treatment. The use of two comparison arms in this study, both TENS and sham treatment, allows for comparisons of experimental device with both TENS as well as sham treatment.

Blinding within this study is a significant strength. All devices are identical in appearance, weight, display, charge time, and sound. It is anticipated that complete blinding of the assessors and patients will be achieved. Care will be taken to limit contact between participants, e.g. schedule participants one at a time so they are not waiting in the same room together. All treatment questions will be directed to the interventionalists, as to maintain blinding of the assessors. Additionally, this protocol outlines concealing the treatment allocation by using opaque envelopes that appear identical. The utilization of a complex randomization schedule is another strength that may ensure equality of treatment groups at baseline. The intent-to-treat analysis may account for unequal dropout between groups and any contamination that may occur.

Potential weaknesses include the possibility of high dropout in one or more treatment arm. To combat this, we are offering incentives and encouraging participants to continue for the entire duration of the study. There is the possibility of a randomization failure, which cannot be overcome. Additionally, due to the nature of the treatment, specifically the differences between the experimental treatment and the TENS treatment, it was not feasible to blind the interventionalist. To address this all interventionalists will undergo strict training and re-standardization based on the treatment protocol. This training will stress treating all patients similarly with regards to demeanor and contact time, regardless of their randomized treatment arm.

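### The sensitivity analysis meant to assess departures from missing at random is, as described, itself a missing-at-random analysis and cannot examine dropout that depends on unrecorded ODI

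*Protocol article*

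**What the plan says.** Under Primary analysis, "a mixed effects linear regression model will be fitted with an unstructured covariance matrix" to ODI at weeks 0, 1, 4, 8 and 12, with week 4 as the primary time point. Under Other considerations, the restricted maximum likelihood analysis is said to be one that "produces approximately unbiased estimates of the treatment effects so long as data are missing at random". The sensitivity analysis is then named as "multiple imputation incorporating baseline and follow-up predictors of outcome", which "will be used to assess the effect of potential violations of the missing at random assumption". The predictors are the only feature given for the imputation. No shift of the imputed values, reference-based rule, pattern-mixture model or selection model is stated.

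The protocol also says what dropout it expects. Primary analysis states: "It is likely that the pattern of dropouts will vary between the study groups". Participants on the most effective intervention are expected to leave later, "while the intervention least effective to have dropouts early on". Outcome measures counts stopping the assigned treatment for lack of efficacy as treatment failure. The Discussion lists high dropout in one or more arms as a possible weakness and adds: "The intent-to-treat analysis may account for unequal dropout between groups and any contamination that may occur".

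**The concern.** The named method and its stated purpose do not match. Imputing from observed predictors fills in a missing ODI value as if the participant resembled those who stayed and had the same recorded history. That is missing at random, conditional on a longer list of variables. Such an analysis shows whether the result depends on which variables are conditioned on. It does not show what happens if people left because of how they were doing at a time when nobody recorded it.

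This matters here because the protocol itself expects dropout to differ by arm with effectiveness, the primary outcome is self-reported, and the only ODI values before the primary time point are those at weeks 0 and 1. If the two analyses agree, the report could present this as robustness to informative dropout that was never examined.

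**Working it through.** **Inputs from the protocol.** Statistical power/Sample size gives a planning difference of 60 − 50 = 10 ODI points, SD 15, two-sided alpha 0.025 and 80% power. The stated size reproduces: n = 2 × 15² × (2.2414 + 0.8416)² / 10² = 42.8, so 43 per arm. The 10 points are used below only as a yardstick. The same section allows 20% dropout, while 38 enrolled and 25 evaluable imply 1 − 25/38 = 34%.

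**Inputs assumed, not in the document.** Missing fractions by arm at the analysed visit, and δ, the number of points by which dropouts are truly worse (higher ODI) than a missing-at-random analysis predicts.

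**Formula.** A missing-at-random analysis puts each arm mean too low by π × δ, where π is the missing fraction. For active minus sham, the bias is π_sham × δ_sham − π_active × δ_active.

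| Assumed case | δ = 5 | δ = 10 | δ = 15 |
|---|---|---|---|
| 10% active, 30% sham, same δ | 0.2 × 5 = +1.0 | +2.0 | +3.0 |
| 30% active, 10% sham, same δ | −1.0 | −2.0 | −3.0 |
| Equal loss, same δ | 0 | 0 | 0 |
| δ in one active arm only, 20% lost | −1.0 | −2.0 | −3.0 |
| δ in one active arm only, 34% lost | −1.7 | −3.4 | −5.1 |

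Lower ODI is better, so a positive bias understates the benefit and a negative bias overstates it.

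**What the planned imputation would show.** This was checked by large-sample simulation with 400,000 per arm. Assumptions: true difference −10, SD 15, and 10% active versus 30% sham missing at week 4. ODI correlations were 0.6 (baseline with week 1), 0.5 (baseline with week 4) and 0.65 (week 1 with week 4). An auxiliary variable correlated 0.6 or 0.8 with week-4 ODI. The primary-type estimate conditions on baseline and week-1 ODI; the imputation adds the auxiliary.

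| What drives dropout | Primary-type estimate | Imputation |
|---|---|---|
| Recorded week-1 ODI | −10.0 | −10.0 |
| Recorded auxiliary outside the ODI model | −9.2 to −8.4 | −10.0 to −9.9 |
| Unrecorded week-4 ODI | −8.0 to −8.1 | −8.3 to −9.0 |

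- In the first row the mixed model already handles the dropout.
- In the second row the imputation exposes and corrects it.
- In the third row the imputation recovers about 0.3 to 0.9 points and stays biased by about 1.0 to 1.7. With the weaker auxiliary the two estimates are −8.04 and −8.32, a gap of 0.3 that would read as agreement.

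The formula confirms the third row. With the weaker auxiliary, sham dropouts were 8.70 and active dropouts 9.06 points worse than imputed: 0.3 × 8.70 − 0.1 × 9.06 = 1.70. The simulated bias was −8.32 − (−10.01) = 1.69.

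These results favour the imputation, because the auxiliary was taken as available for everyone, including dropouts. With equal 20% loss and the same mechanism in both arms, the biases cancelled.

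**The case against.** Four objections deserve weight.

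- **The imputation is not empty.** The trial collects daily pain diaries, device usage logs and rescue acetaminophen counts. If dropout depends on these, missing at random fails for the ODI model but holds for the imputation, which then shows the problem. This stands. A reader might infer that the two analyses must agree whatever the truth; the second and third rows of the simulation show otherwise.
- **Effectiveness-related dropout need not violate missing at random.** The protocol predicts that the timing of dropout will follow effectiveness. It does not say that dropout depends on unrecorded ODI. If a poor response already recorded by week 1 drives it, the mixed model copes. This also stands: the predicted pattern makes a violation plausible but does not establish one.
- **Multiple imputation is a broad framework.** Delta-adjusted imputation is also multiple imputation, the cited source is not at hand, and an analysis plan may give more detail. This stands only in part. The article goes beyond leaving the detail open: it pairs a method, described only by its predictors, with a purpose that this method does not serve.
- **The exposure may be small.** Follow-up is expected to be at its highest at week 4, the endnote targets dropout below 20%, and missed visits are followed up by telephone. The 10% versus 30% split is an illustration, not a forecast. Exposure is probably larger at weeks 8 and 12.

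A reader might also make the Discussion sentence on intent-to-treat a main fault. Analysing people in their assigned arm does not supply missing outcomes, so the sentence is loose. But it is hedged, and it governs no analysis.

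**Conclusion.** The point holds in a limited form. As described, the sensitivity analysis relaxes the missing-at-random assumption by adding predictors; it does not depart from it. Dropout that depends on unrecorded ODI would leave both analyses biased, possibly by similar amounts.

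Under the assumed 10% versus 30% loss and a shift of 5 to 15 points, the bias before any recovery by the imputation is 1 to 3 points, or 10% to 30% of the 10-point planning difference. It is about zero if loss and mechanism are equal across arms. The documents do not support reading this as a bias in favour of the device. If worse unseen outcomes are concentrated in sham, the benefit is understated; if they are concentrated in an active arm, it is overstated.

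The primary model and test are not in question. This is a correction to make to a sensitivity analysis.

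**What to change.** In Other considerations, keep the planned imputation as the base and describe it as a sensitivity analysis to the set of predictors. Then add an explicit departure from missing at random. One suitable form is delta-adjusted imputation, in which imputed ODI is made worse by a stated series of amounts, for example 0, 5, 10 and 15 points. The amounts should vary separately by arm and extend to the tipping point at which the week-4 ODI conclusion changes. A run that imputes active-arm dropouts from the sham arm is optional. If an analysis plan already contains such a step, a cross-reference is enough. The Discussion sentence on intent-to-treat and unequal dropout could be reworded at the same time, but nothing depends on it.

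The cost is a few sentences and a small amount of extra analysis. Design, sample size and primary model do not change.

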## Discussion

Chronic low back pain is a significant issue, resulting in significant costs, lost productivity, and morbidity [1-6]. Therefore, even small improvements in treatment efficacy, particularly for treatments with few side effects, can have a meaningful impact on improving LBP. While there have been some studies assessing the therapeutic effectiveness of TENS, the effect generally is relatively small improvements in chronic LBP as compared to sham treatment. The use of two comparison arms in this study, both TENS and sham treatment, allows for comparisons of experimental device with both TENS as well as sham treatment.

Blinding within this study is a significant strength. All devices are identical in appearance, weight, display, charge time, and sound. It is anticipated that complete blinding of the assessors and patients will be achieved. Care will be taken to limit contact between participants, e.g. schedule participants one at a time so they are not waiting in the same room together. All treatment questions will be directed to the interventionalists, as to maintain blinding of the assessors. Additionally, this protocol outlines concealing the treatment allocation by using opaque envelopes that appear identical. The utilization of a complex randomization schedule is another strength that may ensure equality of treatment groups at baseline. The intent-to-treat analysis may account for unequal dropout between groups and any contamination that may occur.

Potential weaknesses include the possibility of high dropout in one or more treatment arm. To combat this, we are offering incentives and encouraging participants to continue for the entire duration of the study. There is the possibility of a randomization failure, which cannot be overcome. Additionally, due to the nature of the treatment, specifically the differences between the experimental treatment and the TENS treatment, it was not feasible to blind the interventionalist. To address this all interventionalists will undergo strict training and re-standardization based on the treatment protocol. This training will stress treating all patients similarly with regards to demeanor and contact time, regardless of their randomized treatment arm.

## Endnotes

^a^ Based on the ACOEM criteria, this study protocol is intended to provide a high-quality score (Randomization – 1, Blinded Allocation – 1, Baseline Comparability – 1, Patient blinding – 1, Interventionist blinding – 0, Assessor Blinding – 1, Control of co-interventions – 0.5, Compliance – 1.0, Drop Out < 20% – 1, Timing of assessments – 1, ITT analysis – 1 (Total score 9.5/11) High-quality ≥ 8.0.
